#### Statistics and data analysis

All statistical analyses will be performed with a 5 % alpha risk or 95 % confidence interval using SAS 9.3 (SAS Institute, Cary, NC, USA) or SPSS (IBM Statistics, Armonk, NY, USA). No interim analysis will be performed. The normality of quantitative data will be evaluated using a graphical method (frequency histogram and quantile-quantile plot) and a Shapiro-Wilk test [21]. To test the primary hypothesis on PA behavior maintenance, a mixed model procedure will be conducted to take into account the non-independence of the repeated IPAQ measures grouped within participants and the non-independence of the participants grouped in different centers. It should be noted that this type of analysis is highly recommended for repeated measures analysis [39, 48]. The repeated measures will be considered as a longitudinal fixed factor (measurements at T5, T7, T9 and T12). The condition (PAPA vs. SPA) representing the criterion of the analysis will be considered as a fixed effect in the model. The interaction between these two factors will be examined to test whether the change in PA behaviors after the end of the intervention differs depending on the arm of the trial. To control for individual differences in PA levels, the initial level of PA (IPAQ at T0) will be included as a fixed covariate. The intercept will be defined as a random factor that can vary for each participant and for each study center.

For the secondary objectives, we will first check for incomplete or missing data. Missing data at random will be imputed using the multiple imputations method. Sensitivity analyses will be used to address the impact of imputation on conclusions. A general linear model (GLM) will test the hypotheses, including the time of measurement (within-subject factor), the experimental condition (between-subject factor) and the interaction between these two factors.

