### Sample size

The sample size was calculated using the simulation method of PASS 14 software (NCSS, Kaysville, USA) for power analysis with a mixed model. An alpha risk of 5 % and a bilateral hypothesis were taken into account for the power analysis. We estimated the expected scores of the participants in each arm of our study on the basis of the results of large-scale studies [34, 35, 38] that assessed PA behavior maintenance after CR with a questionnaire providing an average score of PA minutes per week. Given the linear effect of time, the change in PA behaviors after SPA suggested that the weekly time spent in PA behavior would be reduced by 5 min very month following the intervention. This result was used to infer the PA level of the group at each measurement point post-program. Several studies have shown that interventions designed to promote maintenance can lead to stabilized or even slightly increased PA behaviors over time (e.g., [2, 29, 34, 38]). We therefore predicted no change in the amount of PA behavior for the PAPA group after the intervention. The power analysis used a similar average score immediately after the intervention of 200 min/week for both groups, a general between-subject variability of 90 min/week, and an autocorrelation of the repeated measures of .55. ([name], [name], [name]. (unpublished manuscript). Testing the effect of text messaging cues to promote physical activity habits: A worksite-based exploratory intervention). The results after 1000 simulations indicated that 50 evaluable participants (25 participants in each arm) would be required to find the time-by-condition interaction effect with an 80 % power level. Assuming about 10 % of patients mistakenly included, lost to follow-up or withdrawing from the study, we randomized 56 participants (28 participants in each of the two arms).

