## Discussion

Cardiovascular patients are generally willing to take part in CR, but unfortunately they do not systematically have the opportunity to do so (80 % of our sample). The PAPA intervention is designed to complement secondary prevention programs or replace them for those who cannot easily participate. The intervention aim is to provide cardiovascular patients with an opportunity to progressively learn, adopt and maintain PA behaviors.

The data from this study will be used to assess the impact of the *As du Coeur* intervention just after the end of the intervention (T5). We do not expect significant differences between the PAPA group and the fully supervised group at this point. Indeed, the fully supervised group will have more supervised sessions that the autonomous group (two per week versus one per week in the second half of the intervention). Based on the linear trend in the PA measures made in the months following the end of the intervention, we expect to find a decline in PA (negative linear slope of the time effect) post-intervention only for the SPA group. We expect that patients of the PAPA group will either maintain the same level (null slope) or even increase their PA (positive slope) in the months following the end of the intervention. Despite our low sample size due to a limited recruitment capacity, it is important to recall that this hypothesis can still be adequately tested with reasonable power using a mixed model approach, as simulation studies of the power in mixed model have shown that it typically increases with repeated measurements [23]. However, we will carry out exploratory analyses to test whether the PAPA intervention also leads to greater automaticity and motivation for PA, higher quality of life and better physical condition compared with the SPA intervention. Another limitation of the study can be the used of the sport motivation scale to assess participant’s motivation in the context of PA as motivation for sport and physical activity can differ.

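### The hypothesis is a difference in linear post-intervention change, but the stated primary test is a 3-df interaction with time as a four-level factor; a 1-df slope contrast should be named as primary

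*Protocol article*

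**What the plan says.** Statistics and data analysis gives the primary model. Time enters as follows: "The repeated measures will be considered as a longitudinal fixed factor (measurements at T5, T7, T9 and T12"). Condition is a fixed effect, IPAQ at T0 is a covariate, and the time-by-condition interaction is the test of interest. On random effects: "The intercept will be defined as a random factor that can vary for each participant and for each study center". The section mentions no linear contrast, random slope or residual covariance structure.

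Sample size plans for the same kind of effect. The sample "would be required to find the time-by-condition interaction effect with an 80 % power level", and "An alpha risk of 5 % and a bilateral hypothesis were taken into account for the power analysis". The expected visit means come from straight lines. For SPA, "the weekly time spent in PA behavior would be reduced by 5 min very month following the intervention". For PAPA, "We therefore predicted no change in the amount of PA behavior for the PAPA group after the intervention". The correlation is given as "an autocorrelation of the repeated measures of .55", with no lag structure.

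The primary objective expects PAPA to decline more slowly and less than SPA. The Discussion puts this in terms of slopes: "we expect to find a decline in PA (negative linear slope of the time effect) post-intervention only for the SPA group", with a null or positive slope in PAPA.

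**The concern.** The article tests one quantity and predicts another. An interaction with a four-level factor asks whether the two arms' profiles differ in any way over T5, T7, T9 and T12. The hypothesis asks whether one straight line falls faster than the other. Testing the second question with the first spreads a 1-df effect over 3 df. It can also give a significant result for a zig-zag pattern that says nothing about maintenance.

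The Discussion speaks of reading a linear slope, so an analyst could reasonably take either test as primary. If the slope is read from a model whose only random effect is the intercept, its standard error is right only when all visit pairs are equally correlated and patients within an arm share one true slope. The word autocorrelation in the sample-size section at least raises the possibility of decay with lag.

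At stake are sensitivity in a trial of about 50 patients, and control of the declared 5% error if the slope is the result reported.

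**Working it through.** **Inputs** (Sample size; Statistics and data analysis): 25 evaluable per arm; SD σ = 90 min/week; correlation ρ = .55; two-sided α = .05; visits at 0, 2, 4 and 7 months after T5; SPA loses 5 min/week per month and PAPA none. The expected PAPA minus SPA differences are therefore 0, 10, 20 and 35 min/week. The T0 covariate is constant within a patient and does not affect these within-patient tests.

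**The plan's own figure.** The stated 80% power is not reproduced by either test, as shown next. Only the step from 50 to 56 reproduces (50/0.9 ≈ 56).

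**Power, exchangeable .55.**
- Mean visit time is 3.25 months, so Sxx = 3.25² + 1.25² + 0.75² + 3.75² = 26.75.
- Within-patient variance: σ²(1 − ρ) = 8100 × .45 = 3645.
- SE of the slope difference: √(2 × 3645 / (25 × 26.75)) = √10.90 = 3.30.
- 1-df test: noncentrality 5 / 3.30 = 1.514; noncentral t on 48 df gives **32%**.
- 3-df test: the differences, centred at 16.25, have sum of squares 668.75. Noncentrality is (25/2) × 668.75 / 3645 = 2.29, which is 1.514². Noncentral F on 3 and 144 df gives **21%**.

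The signal is the same in both tests; the loss comes only from spreading it over 3 df. For 80% power the 3-df test needs 120 per arm and the linear test 87 (120/87 = 1.38, so 38% more). If the slope difference is set at 9.45 min/week per month, where the linear test has 80% power with 25 per arm, the 3-df test has 65%.

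**Power, AR(1) .55 per visit, covariance modelled correctly.** 3 df: **12.5%**. Linear: **18%**.

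**Type I error of the linear contrast in a random-intercept model.** Under AR(1) .55 per visit the correlations are .55, .3025 and .1664 at lags 1, 2 and 3.
- True SE of the slope difference: 4.75.
- The model instead uses the average correlation, (3 × .55 + 2 × .3025 + .1664)/6 = .404. Its SE is √(2 × 8100 × .596 / (25 × 26.75)) ≈ 3.80.
- The ratio 3.80/4.75 = 0.80 means the t statistic is too large by a quarter.

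Simulated type I error at nominal 5%, 60,000 or more balanced trials per scenario:

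| Covariance | Linear contrast, random intercept | 3-df test, random intercept | Test on per-patient slopes |
|---|---|---|---|
| Exchangeable .55 | 5.0% | 5.1% | 5.0% |
| AR(1) .55 per month | 8.0% | 5.2% | 5.1% |
| AR(1) .55 per visit | 11.8% | 5.9% | 5.1% |
| Exchangeable + slope SD 2 (assumed) | 5.2% | 4.9% | 4.9% |
| Exchangeable + slope SD 5 (assumed) | 6.4% | 5.1% | 5.0% |
| Exchangeable + slope SD 10 (assumed) | 9.7% | 5.4% | 5.1% |

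Slope SDs are in min/week per month. The article gives none, so the range is an assumption.

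**The case against.** **The sample-size section does not specify a directional 1-df slope test.** This stands. It states a bilateral hypothesis and an interaction effect, and uses the linear decline to generate visit means. The sample-size and analysis sections therefore both name an interaction. The mismatch is between that interaction and the linear shape of the hypothesis.

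**The two harms are alternatives.** This stands too. A reader might infer that the plan both loses power and inflates type I error. It does not. If the 3-df test is primary, power is lost and the error rate stays near 5% to 6%. If the slope contrast is primary, the omnibus loss disappears and the error rate becomes the question.

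**The inflation is conditional.** A reader might infer that a slope read from this model necessarily exceeds 5%. The article does not support that: it gives no lag structure for the .55 and no slope variance. A residual covariance could also be set in an analysis plan not shown, and its absence from a journal article is not in itself a fault.

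**The power gain depends on the correlation.** Under AR(1) per visit it is about 5 to 6 points instead of 11. In that case the 3-df test in the stated random-intercept model rejects 17.7% of the time, about the same as a valid slope test, although at a 5.9% error rate.

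**Time as a factor is defensible**, since it does not impose linearity. That is a reason to keep it as a supporting analysis. A covariance choice made elsewhere would not settle which test is primary.

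**Conclusion.** The point holds as a mismatch between the tested interaction and the linear hypothesis, and correcting it is a cheap improvement. With exchangeable correlation the stated test gives up about 11 points of power (21% against 32%) at the article's own inputs. With AR(1) per visit, correctly modelled, it is 12.5% against 18%.

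The error-rate part is a risk that applies only if the slope is read from a model with no more than a random intercept, and only if the covariance departs from compound symmetry: about 8% to 12% under the AR(1) readings of .55, and about 5% to 10% over the assumed slope SDs.

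Neither test comes near the stated 80% power. That is a separate problem with the sample size, and changing the test does not solve it.

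**What to change.** State one primary test: the two-sided 1-df linear time-by-condition contrast, with visits scored 0, 2, 4 and 7 months after T5. Allow a random slope or an unstructured residual covariance for the four visits, with a small-sample degrees-of-freedom method such as Kenward-Roger. Report the 3-df interaction as a check of linearity.

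The cost is a sentence or two in the protocol or analysis plan and standard software options; no new visits, data or patients are needed. The downsides are a few more covariance parameters to estimate from about 50 patients, and less sensitivity to a difference that is not linear, which the retained 3-df test partly covers.

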## Discussion

Cardiovascular patients are generally willing to take part in CR, but unfortunately they do not systematically have the opportunity to do so (80 % of our sample). The PAPA intervention is designed to complement secondary prevention programs or replace them for those who cannot easily participate. The intervention aim is to provide cardiovascular patients with an opportunity to progressively learn, adopt and maintain PA behaviors.

The data from this study will be used to assess the impact of the *As du Coeur* intervention just after the end of the intervention (T5). We do not expect significant differences between the PAPA group and the fully supervised group at this point. Indeed, the fully supervised group will have more supervised sessions that the autonomous group (two per week versus one per week in the second half of the intervention). Based on the linear trend in the PA measures made in the months following the end of the intervention, we expect to find a decline in PA (negative linear slope of the time effect) post-intervention only for the SPA group. We expect that patients of the PAPA group will either maintain the same level (null slope) or even increase their PA (positive slope) in the months following the end of the intervention. Despite our low sample size due to a limited recruitment capacity, it is important to recall that this hypothesis can still be adequately tested with reasonable power using a mixed model approach, as simulation studies of the power in mixed model have shown that it typically increases with repeated measurements [23]. However, we will carry out exploratory analyses to test whether the PAPA intervention also leads to greater automaticity and motivation for PA, higher quality of life and better physical condition compared with the SPA intervention. Another limitation of the study can be the used of the sport motivation scale to assess participant’s motivation in the context of PA as motivation for sport and physical activity can differ.

As this study will show whether the PAPA intervention promotes physical activity maintenance in people with CVD, it has potentially significant implications for the management of cardiovascular patients. If successful, it will increase PA behaviors and hence reduce medical costs and enhance the quality of life of people with CVD over the long term. In addition to improving health outcomes in the short and long runs, this intervention has the potential to reduce the public health costs of cardiac rehabilitation. It therefore may prove to be a feasible addition to existing health services and could be delivered to people with CVD who have already attended CR programs as a “transition” program.

## Abbreviations

CR, cardiac rehabilitation; CVD, cardiovascular disease; PA, physical activity; PAPA, progressive autonomy; SPG, supervised physical activity
